### Procedures

2.7

CPO staff and/or UIC study staff approach potential participants using an interest form which collects contact information. UIC study staff recruit potential participants by confirming eligibility, gathering informed consent, and registering them for a workshop. Groups of participants are randomly assigned to complete 1 of 8 intervention workshop conditions at a CPO site for 1 or 2 days (Fig. 3). All receive the constant component. Groups randomized to receive one additional component attend a one-day workshop, and groups randomized to receive two or more additional components attend a two-day workshop (see conditions in Fig. 1). Each participant receives between $100 and $220 depending on the condition they are randomized to and whether selected for a focus group discussion. Compensation includes $25 for each workshop session attended; our formative research highlighted the importance of compensating participants for their time attending sessions, not just completing assessments [17]. Compensation also includes $5 to cover transport for study activities [17].

**Fig. 3 fig3:**
[figure not shown]
Schema for the pilot optimization trial of Floreciendo.

Prior to the workshop start, teens and caregivers complete a baseline questionnaire. Teens also provide a urine sample to be tested for three common STIs: gonorrhea, chlamydia, and trichomoniasis. Urine samples are tested in a lab using a PCR test, and teens are called with their results when they are received by the study team (typically within 2–3 business days). Immediately after each workshop session, participants complete a brief feedback survey on the session's acceptability. After finishing all sessions per their condition, participants complete a comprehensive feedback survey about the acceptability, appropriateness, and feasibility of the sessions. Breakfast, lunch, and childcare are provided at the workshop, based on feedback received during formative research [17]. Approximately 6 months later, caregivers and teens are asked to complete a follow-up questionnaire, and teens are asked to provide another urine sample for STI testing. While questionnaires can be completed remotely, STI testing for teens is done in person and uses the same procedures as at baseline.

Teens who test positive for an STI at baseline or follow-up are offered treatment for themselves and their partner from an adolescent medicine physician, paid for by the study. In line with the Centers for Disease Control's recommended regimen for gonorrhea and alternative regimens for chlamydia and trichomoniasis [31], single treatment regimens with directly observed therapy are offered to increase medication adherence. Alternative regimens are used if participants have allergies. When providing treatment, the adolescent medicine physician counsels teen participants on ways to prevent reinfection. The physician also recommends that the participant follow up with their primary care provider or offers recommendations of providers to establish care.

Floreciendo facilitators are invited to complete surveys after receiving facilitator training (described below) to provide feedback on the training and how it could be improved. Additionally, facilitators, CPO leadership, UIC staff, and Floreciendo collaborators (e.g., Community Advisory Council members) are invited to complete implementation surveys near the time of intervention delivery completion (estimated to be about 18 months after study start) or before staff turnover. These surveys measure the acceptability, appropriateness, and feasibility of the intervention and its implementation. CPO facilitators and leadership surveys also measure intentions to adopt and sustain the intervention.

### Facilitator training

2.8

Based on formative research informing the current study [14], facilitators delivering Floreciendo must be Latina, fluent in English and/or Spanish, and identified from within the CPOs. Where possible, facilitators are paired with teens or caregivers to facilitate similar age or experience with motherhood. At least one facilitator per workshop is bilingual. Facilitators are trained by UIC staff. Initial training of facilitators lasts approximately 18 h, with two full days of in-person sessions and the remaining sessions occurring remotely. Facilitators who are trained after the study start receive one full day of in-person sessions and remote sessions and are asked to observe a full workshop. Based on best practices [32], trainers follow a standardized training manual and protocol and provide ongoing support and consultation. Training content covers the objectives and content of all sessions, tips in facilitation (e.g., in addressing challenging group dynamics), the importance of fidelity, and how to manage disclosure of suicidality and abuse. Modeling, role-play, and discussions are used to reinforce learning and to build a sense of community among facilitators. As part of their training, facilitators are also required to complete Sex Ed To-Go modules on STIs, pregnancy prevention (including abstinence), healthy relationships, and communication skills [33].

### Ethical considerations and safety monitoring

2.9

The study protocol has been approved by the Institutional Review Board at the University of Illinois Chicago. Written informed consent is obtained from teens aged 18 years and female caregivers. Written teen assent and parent permission is required for teens who are minors (i.e., ages 14–17 years old). Teens’ refusal supersedes parent permission. The principal investigator oversees potential social harms reported by teens in partnership with leadership staff at CPOs. On surveys, teens are flagged if they report any intimate partner violence in the past year, any thoughts of suicide in the past two weeks, or poor wellbeing. Flagged teens are discreetly escorted to a designated CPO staff member, who is trained to assess harm severity and facilitate safety planning. Disclosures of abuse, violence, or significant harm to self or others are recorded and reported to appropriate authorities. A data and safety monitoring board meets annually to oversee participant safety.

### Sample size

2.10

As is appropriate for pilot studies, this study aims to understand the feasibility and acceptability of running an optimization trial and thus is not explicitly powered to detect statistically significant effects [34]. However, we will conduct exploratory analyses of intervention component effects on effectiveness outcomes, proximal behavioral outcomes, and theoretical mediators (detailed below).

### Outcomes

2.11

#### Primary outcomes

2.11.1

Our primary outcomes are: 1) feasibility of using a factorial design, and 2) acceptability of the intervention components. We will assess the feasibility of using a factorial design by measuring the proportion of conditions implemented according to their randomization schedule (benchmark is ≥ 90 %). We will also examine the proportion of dyads who complete all sessions specified per their condition (benchmark is ≥ 80 %) and the proportion who complete baseline assessments (benchmark is ≥ 80 %) and follow-up assessments (benchmark is ≥ 70 %). We will assess the acceptability of the Floreciendo intervention components—i.e., the extent to which participants perceive the components to be agreeable, palatable, or satisfactory [35]—by measuring the proportion of teens and caregivers who report high satisfaction with the intervention components. We will measure acceptability using items adapted the mHIST [36] (benchmark is ≥ 80 % agreement).

#### Exploratory effectiveness outcomes

2.11.2

While this pilot study is not powered to estimate effects of the components [34], it provides an opportunity to explore the potential for effectiveness in a future, adequately powered trial. To this end, we will assess teens’ risky sexual behavior by measuring the proportion of teens who report risky sexual behavior at follow-up, self-reported using AIDS Risk Behavior Assessment [37]. We anticipate this will serve as our primary effectiveness outcome in our future optimization trial. Our secondary outcomes in the future optimization trial will include STIs and unplanned pregnancy. In this pilot, we will measure the proportion of teens who screen positive for any of three STIs and the proportion of teens with an unplanned pregnancy (based on self-report) at follow-up. Where sample sizes allow, we will explore mediators and proximal behavioral outcomes in line with our conceptual model, including mental health, teen-caregiver relationships, substance use, IPV exposure, sexual relationship power, and gender equitable norms.

#### Exploratory implementation outcomes

2.11.3

In addition to examining the acceptability of the intervention components (described above), we will explore other implementation outcomes of Floreciendo, in line with Proctor et al.‘s implementation outcomes framework [35]:•*Feasibility*: The extent to which Floreciendo can be successfully carried out in this setting (distinct from the feasibility of using a factorial design described above);•*Appropriateness*: The extent to which participants believe Floreciendo to be relevant or compatible with the setting and Latina community;•*Adoption*: The proportion of CPOs willing to initiate Floreciendo;•*Sustainability*: The intention of the CPOs to maintain or institutionalize Floreciendo;•*Cost*: Costs associated with the implementation of Floreciendo;•*Fidelity*: The extent to which Floreciendo is implemented as intended.

We will quantitatively measure acceptability, feasibility, and appropriateness of the intervention components (i.e., the intervention content and implementation strategies) among participants (i.e., teens and caregivers) and facilitators/staff/collaborators using items adapted from the mhIST [36]. Among facilitator/staff/collaborators, we will measure adoption using items adapted from the Antiretroviral Treatment Access Study (ARTAS) [38] and sustainability intentions using items adapted from the Program Sustainability Assessment Tool (PSAT) [39]. We will track costs associated with intervention delivery (e.g., personnel costs, workshop supplies) to get an early indication to inform the future optimization trial.

We will assess fidelity by measuring facilitator and observer ratings of adherence [[40], [41], [42]], quality of delivery [[40], [43]], and participant responsiveness [[32], [44]]. Fidelity forms will be reviewed regularly by an experienced trainer on the study team and the CPO site supervisor to provide feedback. Facilitators who are not reaching ≥80 % fidelity will be required to receive additional training.

### Qualitative data collection

2.12

We aim to conduct about four focus group discussions with Latina teens, four with female caregivers, and two with facilitators, each lasting approximately 90 min. We will recruit about 6–8 participants per focus group. Additionally, we aim to conduct roughly six 30-min key informant interviews with CPO leadership and other collaborators (e.g., Community Advisory Council members). Focus groups and interviews will be hosted in person at a location convenient (e.g., a private room at a CPO) or remotely (e.g., Zoom) using a semi-structured guide. Open-ended questions will build on the quantitative survey questions to explore perceived effects of the workshop on participants and perceptions of implementation outcomes. Focus groups and interviews will be conducted in English or Spanish, digitally recorded, translated as needed, and transcribed.

### Retention

2.13

At enrollment, we will obtain contact information from participants, including of at least two people who could help us locate participants. We will ask participants for their permission to send them study material and reminders via text messages. If more than three contact attempts fail, we will reach out to the contacts from participants' records, request assistance from the recruiting CPO, visit the family's last known address, and leave letters at the home encouraging call-back. Remuneration for participants' time completing surveys will increase from $30 at baseline to $35 at follow-up to support retention.

### Data management

2.14

Data management will be housed in REDCap, a password-protected and user-restricted application [45]. Exported participant data, linked by an assigned numerical ID, will be stored in secure servers maintained by UIC. Teen participants are also assigned a medical record number, used to label their urine samples. After screening the urine for STIs, the laboratory adds teen participants’ STI results directly to their electronic medical record using the medical record number; this is how STI test results are shared with the study team and the adolescent medicine physician providing treatment. The principal investigator will review any requests to use the data externally, and data shared will be stripped of identifiers.

### Analyses

2.15

We will assess the feasibility of using a factorial design and acceptability of intervention components using descriptive statistics. To explore effectiveness outcomes in support of our move towards running a fully powered optimization trial, we will conduct an intention-to-treat analyses. We will use mixed-effects models for continuous outcomes and generalized estimating equations for binary outcomes. We will examine the mean difference in risky sexual behavior scores (primary outcome) for each intervention component from baseline to follow-up. Where sample sizes allow, we will do the same for STI incidence and unplanned pregnancy. Each experimental factor will be coded at two levels using effect coding (“on” = 1; “off” = −1) [19]. We will replicate analyses to look at component effects on theoretical mediators and proximal behavioral outcomes and explore the possibility of examining mediation effects and interactions between components.

For exploratory implementation outcomes, we will conduct descriptive analyses to summarize quantitative measures from participant and facilitator/staff/collaborator implementation surveys, as well as the facilitator and observer fidelity forms. We will use the *planning for and assessing rigor in rapid qualitative analysis (PARRQA)* rapid qualitative analysis framework [46] to analyze open-ended responses, focus group discussion transcripts, and key informant interview transcripts. Data will be sorted using a matrix, with relevant data extracted and key themes refined through extensive discussion among the analysis team and in consultation with the project's Community Advisory Council.

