**Methods:**

This protocol describes a hybrid type 2 mixed-methods study with a pilot 2^3^ factorial experimental design which draws on the multiphase optimization strategy (MOST) framework. Small groups of teen-caregiver dyads (target n = 92 dyads/184 participants) will be randomized to 1 of 8 conditions across four CPOs. All will receive the Foundations in Sexual Risk Prevention (i.e., constant) component. Groups of dyads will be randomized to different combinations of three intervention components of Floreciendo, which are either “on” or “off”: 1) Condoms and Contraception, 2) Family Strengthening, and 3) Gender and Relationships. Our aim is to examine the feasibility of using a factorial design and the acceptability of the intervention components. We will also explore effectiveness outcomes—including risky sexual behavior (primary) and incidence of sexually transmitted infections and unplanned pregnancy (secondary)—and implementation outcomes, including appropriateness, feasibility, adoption, sustainability, cost, and fidelity. Qualitative data will build on quantitative data. We will conduct focus group discussions and key informant interviews with Latina teens, female caregivers, facilitators, CPO leadership, and collaborators.

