### Study design

2.1

This is a hybrid type 2 effectiveness – implementation mixed methods study and uses a 2 × 2 × 2 (or 2^3^) factorial experimental design for the pilot optimization trial. We chose a hybrid type 2 design given that we aim to run a fully powered optimization trial with equal interest in effectiveness and implementation outcomes [24] and given that we adapted Floreciendo from an evidence-based program [15,16]. We chose to pilot a factorial trial design given our ultimate goal of optimizing the Floreciendo intervention using the MOST framework [19]. We decided on a mixed methods approach to facilitate a deeper understanding of exploratory effectiveness and implementation outcomes than would be possible with either method alone [25].

All dyads of Latina teens and their female caregivers receive the first of the four intervention sessions of Floreciendo (i.e., the “constant,” Foundations in Sexual Risk Prevention). Dyads are randomized to receive different combinations of the remaining three sessions which are either delivered (i.e., “on”) or not delivered (i.e., “off”): Condoms and Contraception, Family Strengthening, and Gender and Relationships. The study design therefore includes eight experimental conditions. Sessions are led by trained staff at each CPO. To facilitate easier communication about the conditions and enhance adherence to condition delivery [26], our Community Advisory Council chose to name each condition after a popular food in Latine culture, on a scale from most complex (i.e., chilaquiles) to simplest (i.e., maiz) (Fig. 1). In using a factorial design, there is no typical control condition; that is, participants are used in the estimation of all main effects and interactions [27].

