**Fig. 1 fig1:**
[figure not shown]
Conditions and planned number of Floreciendo workshops.

We plan to enroll about 92 dyads (ñ184 participants total). Floreciendo is designed to be delivered in small groups of roughly 3–5 dyads. To achieve our planned sample size, we expect to deliver about 24 workshops. Our optimization objective [20] is to arrive at the best expected outcome among all active conditions (i.e., with no time or cost restrictions on the number of factors which can be “on”). This objective was determined through our formative Floreciendo research, whereby no specific constraints (i.e., limitations on cost or time) for delivering the intervention were raised by Latina teens, female caregivers, or CPO staff/leadership [17]. We will collect qualitative data after collecting quantitative data, with greater emphasis placed on the quantitative data (i.e., using a QUANT → qual design) [25].

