### Randomization and masking

2.6

Given the large number of conditions [30], the randomization schedule is generated prior to the study start by the study statistician and organized in Excel. Groups of dyads are randomly assigned to 1 of 8 conditions (Fig. 1) in blocks of 8. Conditions are revealed line by line as the recruitment of each group of dyads occurs. The Floreciendo Project Director manages the randomization schedule and communicates assignments to CPO sites. Each CPO has an equal chance of delivering any condition, and each intervention component will be delivered a roughly equal number of times by the study end. Facilitators at each CPO are trained in delivering all intervention components given the relatively small sample size, as it would not be feasible for each CPO to deliver all eight conditions.

CPO and UIC staff are blinded to the condition when approaching and recruiting participants. Only key UIC staff, facilitators, and CPO supervisors are aware of the condition for the purposes of delivering the workshop and are informed not to disclose the condition to participants prior to the workshop. Teens and caregivers are informed of their condition just before the workshop starts and are asked not to discuss their condition assignment with anyone outside of their group. To measure possible contamination, participants are asked on follow-up surveys the extent to which they discussed content received in their condition with participants randomized to other conditions.

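### About 24 workshop groups are randomised, but section 2.1 says dyads are and section 2.15 ties neither model to the group, so exploratory component-effect intervals may be too narrow

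*Protocol article*

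**What the plan says.** **Unit of randomisation.** Three places in the protocol article name the group. The abstract (Methods) has "Small groups of teen-caregiver dyads (target n = 92 dyads/184 participants) will be randomized to 1 of 8 conditions across four CPOs". Section 2.6 has "Groups of dyads are randomly assigned to 1 of 8 conditions (Fig. 1) in blocks of 8". Section 2.7 also assigns groups of participants to the eight workshop conditions. Section 2.1 differs: "Dyads are randomized to receive different combinations of the remaining three sessions".

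**Number and size of groups.** The text under Fig. 1 plans small groups of roughly 3–5 dyads and states: "To achieve our planned sample size, we expect to deliver about 24 workshops".

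**Analysis.** Section 2.15 specifies intention-to-treat, effect coding of the three components as +1/−1, a mean difference per component from baseline to follow-up, and the model families: "We will use mixed-effects models for continuous outcomes and generalized estimating equations for binary outcomes". It does not say whether the random effect or GEE cluster is the teen, the dyad or the workshop group.

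**Status.** Sections 2.10 and 2.11.2 call the component effects exploratory and the pilot unpowered for them. The primary outcomes (section 2.11.1) are feasibility and acceptability benchmarks, analysed descriptively.

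**The concern.** Condition is allocated and delivered to a whole workshop group, and the sessions are interactive. Outcomes of teens in one group may therefore be correlated, and each component contrast compares groups.

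The only repeated structure visible in section 2.15 is baseline and follow-up within a teen. Mixed models and GEE as worded are both satisfied by clustering on the teen, and section 2.1 would seem to support that choice. Correlation within the randomised unit would then be left out.

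Naming the group does not by itself settle the GEE analyses. The usual sandwich variance is biased downwards with few clusters, and 24 is few.

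At stake are the intervals for the component effects on risky sexual behaviour, mediators and proximal outcomes. In a pilot without power, those intervals are much of what these analyses can offer. The article says the results will inform plans for a fully powered optimisation trial. That trial will need a workshop-group ICC, which a teen-only model does not estimate.

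**Working it through.** **1. The plan's own figures.** 92 dyads in groups of 4 (midpoint of 3–5) need 92/4 = 23 workshops. The stated figure of about 24 is three full blocks of 8. It allows 24 × 3 = 72 to 24 × 5 = 120 dyads, which brackets 92, and 92 × 2 = 184. The figures agree. If balanced, there are 24/8 = 3 groups per condition, so 12 on and 12 off per component.

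**2. Inputs.** Teens per group: 92/24 = 3.83 at enrolment. At the 70% follow-up benchmark, about 64 teens remain, or 2.68 per group. The ICC is not in the article; 0 to 0.20 is an assumption.

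**3. Design effect if groups are ignored.** DE = 1 + (m − 1) × ICC, and the error of a nominal 5% z-test is 2 × [1 − Φ(1.96/√DE)].

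| ICC | DE, m = 3.83 | Error | DE, m = 2.68 | Error |
|---|---|---|---|---|
| 0.05 | 1.14 | 6.7% | 1.08 | 6.0% |
| 0.10 | 1.28 | 8.4% | 1.17 | 7.0% |
| 0.20 | 1.57 | 11.7% | 1.34 | 9.0% |

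The right-hand columns are slightly optimistic. With random loss, a retained teen has on average 0.7 × 2.83 = 1.98 retained group-mates, not 1.68.

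**4. Simulation.** Balanced 2³ design, 24 groups, 92 teens, normal outcome at one time point, main-effects model, 5,000 runs per cell. The Monte Carlo standard error near 9% is √(0.09 × 0.91/5000) = 0.4 percentage points. Type I error is 100% minus coverage of the 95% interval; each cell shows full follow-up / 70% follow-up.

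| ICC | Groups ignored | Group sandwich, z-limits | Sandwich × 24/20, t on 20 df |
|---|---|---|---|
| 0 | 4.6 / 4.8% | 8.6 / 9.1% | 4.9 / 5.5% |
| 0.02 | 6.3 / 5.7% | 9.2 / 9.6% | 5.6 / 5.4% |
| 0.05 | 7.6 / 6.6% | 9.5 / 10.1% | 5.6 / 5.4% |
| 0.10 | 8.6 / 7.8% | 8.9 / 9.6% | 5.0 / 5.7% |
| 0.20 | 12.4 / 10.2% | 8.9 / 9.5% | 4.9 / 5.3% |

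**5. Binary outcome.** With a 30% outcome, 70% follow-up, identity link and 3,000 runs, ignoring groups gives 6.1%, 7.9% and 10.3% at ICC 0.05, 0.10 and 0.20. The uncorrected group sandwich gives 9.2–10.2%, including 10.2% at ICC 0. Kauermann-Carroll with t-limits gives 4.9–5.8%. A further run at 70% follow-up over ICC 0–0.20 gave 5.1–11.5%, 9.0–10.9% and 5.0–6.5% for the same three methods.

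**6. Mixed model with a group intercept.** A REML random intercept for workshop with plain z-limits, at 70% follow-up and follow-up values only, gives 5.6–5.8% over ICC 0–0.20.

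**7. Width of a sound interval.** Relative to a z-interval that ignores groups, the ratio is √DE × 2.086/1.96, with t on 24 − 4 = 20 df. At ICC 0.01, 0.05, 0.10 and 0.20 it is 1.08, 1.14, 1.21 and 1.33 (m = 3.83), or 1.07, 1.11, 1.15 and 1.23 (m = 2.68).

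**The case against.** **A reader might infer that the plan excludes the group and that the intervals will be too narrow.** The article supports neither. Mixed models and GEE are standard for clustered data, both can take the workshop as cluster, and section 2.15 does not say it is left out. Individual-level analysis with the right clustering is valid. The size of any shortfall depends on an ICC and a variance estimator the article does not give.

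**Such detail belongs in the full protocol or SAP.** This largely stands for the variance estimator and degrees of freedom, so their absence alone is no finding. It does not cover the randomised unit, which the article states in two ways and then omits from an analysis section that gives the contrast and the coding.

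**A small-sample correction matters little for the mixed model.** This stands: 5.6–5.8% without one once the group intercept is in. The need for a correction is specific to GEE with a sandwich variance.

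**The relevant ICC is that of change.** Baseline precedes the workshop, so stable differences between groups partly cancel. This is fair and may put the ICC low in the range. Correlation arising in the workshop would not cancel.

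**Site imbalance.** Because section 2.6 describes blocking without stratification by community partner organisation, one might want a site term. Figures for imbalance need a number of workshops per site, which the article does not state. Chance imbalance under valid randomisation is not an error, and covariate choice can be left to the SAP.

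**The analyses are exploratory.** This stands, and it limits the weight of the point.

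**Conclusion.** The point holds in a conditional form. The article is inconsistent about the randomised unit, and section 2.15 can be followed to the letter without accounting for the workshop group.

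- If the models cluster only on the teen, type I error for a component effect is about 7–12% at an assumed ICC of 0.05–0.20. The top of that range is at full follow-up; at 70% follow-up the simulated values are about 7–10%. At an ICC near 0 nothing is lost.
- If GEE clusters on the group with the uncorrected sandwich and z-limits, the error is about 9–11% at any ICC from 0 to 0.20.
- With the group modelled and a small-sample method for GEE, the error is about 5–6.5%.

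These figures assume 24 balanced groups, a main-effects model and outcomes at a single time point. The feasibility and acceptability outcomes are descriptive and need no group-clustered intervals on this account. This is a worthwhile, inexpensive improvement to exploratory analyses, not a defect that threatens the pilot's main conclusions.

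**What to change.** 1. In section 2.1, say that groups of dyads are randomised, in line with the abstract and sections 2.6 and 2.7.
2. In section 2.15, name the workshop group as the cluster for component effects:
   - continuous outcomes: a random intercept for workshop group, plus one for teen if both time points are modelled;
   - binary outcomes: GEE clustered on workshop group, with a small-sample corrected variance such as Kauermann-Carroll and t-limits on the number of groups minus the number of parameters (20 df for main effects only; 24 − 8 = 16 if all interactions are fitted).
3. Report the workshop-group ICC with its confidence interval for planning the next trial.

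The cost is a change of wording and wider intervals: about 1.1 to 1.3 times those of a z-based analysis that ignores groups, over the assumed ICC range. No change to recruitment, delivery or data collection is needed.

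### The exploratory component effects are framed as change from baseline; adjusting the follow-up value for baseline is at least as precise and costs almost nothing

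*Protocol article*

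**What the plan says.** Section 2.15 (Analyses) sets the effectiveness contrast for risky sexual behavior as the "mean difference in risky sexual behavior scores (primary outcome) for each intervention component from baseline to follow-up". It then adds: "Where sample sizes allow, we will do the same for STI incidence and unplanned pregnancy". The models named are "mixed-effects models for continuous outcomes and generalized estimating equations for binary outcomes", under the statement that "we will conduct an intention-to-treat analyses". The section does not mention the baseline value as a covariate. It also does not say whether change scores or both time points are modelled.

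Section 2.7 (Procedures) has the baseline questionnaire completed before the workshop and a follow-up questionnaire about 6 months later. Section 2.11.1 sets a 70% benchmark for completing follow-up. Section 2.11.2 gives the same outcome on another scale, as the "proportion of teens who report risky sexual behavior at follow-up, self-reported using AIDS Risk Behavior Assessment". Sections 2.10 and 2.11.2 say that the pilot is not powered for component effects, which are explored to inform the later optimization trial.

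**The concern.** Taken at its word, the stated contrast subtracts baseline from follow-up and compares the differences between the on and off levels of each component. That gives baseline a fixed weight of one, whatever its actual correlation with follow-up. A randomised comparison does better when the weight is estimated, that is, when follow-up is adjusted for baseline. Two things are at stake.

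- **Precision.** Intervals become wider than necessary in a trial that is already small.
- **Chance imbalance.** Whole workshop groups are randomised (section 2.6), about 12 against 12 for each component, so baseline gaps will be common. A change score over-corrects for them whenever the correlation is below 1.

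A third, conditional matter is loss to follow-up. The benchmark tolerates up to 30% loss. If that loss depended on baseline behaviour in one way at the on level and another at the off level, some versions of a change analysis would be biased where a baseline-adjusted analysis would not.

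**Working it through.** **Inputs from the article.** The Abstract gives "target n = 92 dyads/184 participants", so 92/2 = 46 teens per level of each component if balanced. The text under Fig. 1 says "we expect to deliver about 24 workshops", so about 12 groups per level and 92/24 = 3.83 dyads per group. At 70% follow-up, 46 × 0.7 = 32.2 teens per level remain. There is no power calculation to reproduce.

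**Assumptions.** The article gives no correlation ρ, intraclass correlation (ICC), SD or pattern of loss. All are assumed below. Steps 1 and 2 take equal variance at both time points and ignore clustering and the single degree of freedom spent on the baseline slope.

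**1. Variance of the contrast, in units of SD².** Change score: 2(1−ρ). Follow-up alone: 1. Follow-up adjusted for baseline: 1−ρ². The ratio of adjusted to change is (1−ρ²)/[2(1−ρ)] = (1+ρ)/2.

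| ρ | Change | Adjusted | Ratio | Extra teens needed by change |
|---|---|---|---|---|
| 0.3 | 1.40 | 0.91 | 0.65 | 54% |
| 0.5 | 1.00 | 0.75 | 0.75 | 33% |
| 0.7 | 0.60 | 0.51 | 0.85 | 18% |

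Below ρ = 0.5 the change score is less precise than ignoring baseline altogether.

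**2. Minimum detectable difference** (two-sided 5%, 80% power): (1.96 + 0.84) × √(2v/32.2), where v is the variance from step 1. For ρ = 0.3, 0.5 and 0.7, the change score gives 0.83, 0.70 and 0.54 SD. The adjusted analysis gives 0.67, 0.60 and 0.50 SD. Clustering would enlarge both.

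**3. Chance imbalance.** The SD of the baseline gap is √[(2/46)(1 + 2.83 × ICC)], which is 0.22 at ICC 0.05 and 0.26 at ICC 0.20. The probability of a gap above 0.25 SD in either direction is 26% and 34%. With no component effect, a gap g produces an expected difference in change of −(1−ρ)g. For g = 0.25 and ρ = 0.5, that is −0.125 SD.

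**4. Loss to follow-up, scores, no component effect.** If selective loss lowers the mean baseline of retained teens by m at one level only, their mean follow-up falls by ρm and their change is off by (1−ρ)m. For an assumed m = 0.2 SD, this is 0.14, 0.10 and 0.06 SD at ρ = 0.3, 0.5 and 0.7. Simulation with 30% loss at the on level and 28% at the off level gave the same figures for completers' change. It gave about 0.01 SD or less for a likelihood mixed model that keeps every baseline, and for baseline adjustment. If loss depends on baseline equally at both levels, m cancels.

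**5. Loss to follow-up, binary, no component effect.** Assume 30% risky at baseline, with follow-up risk 65% in those teens and 20% in the rest. At the on level, 50% of risky teens and 21.43% of the others are lost. At the off level, 30% are lost regardless. Total loss is 30% at both levels (0.3 × 0.5 + 0.7 × 0.2143 = 0.30).

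- Retained at on: 0.15/0.70 = 21.4% risky at baseline, and 0.214 × 0.65 + 0.786 × 0.20 = 29.6% at follow-up.
- Retained at off: 30.0% at baseline, and 0.3 × 0.65 + 0.7 × 0.20 = 33.5% at follow-up.
- Completers' change: +8.2 against +3.5 points, a log odds ratio of +0.27 (simulated +0.26).
- Generalized estimating equations (GEE) with all baselines kept and independence working correlation: [logit 0.296 − logit 0.30] − [logit 0.335 − logit 0.30] = −0.18 (simulated −0.20).
- GEE with all baselines kept and exchangeable correlation: simulated −0.04.
- Follow-up adjusted for baseline: 0, because risk within each baseline group is the same at both levels (simulated −0.02, standard error about 0.02).

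When loss depends on baseline equally at both levels, the simulated GEE component effect was 0.016 (independence) and 0.012 (exchangeable), with standard error about 0.02, so in effect zero.

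**The case against.** The best defence is that the sentence does not rule out a good analysis. Scores go to a mixed-effects model. Such a model, fitted by likelihood to both time points with baseline means constrained equal, also reports a baseline-to-follow-up mean difference. It handles loss that depends on observed baseline. A condensed article may leave covariates and missing-data handling to the full plan. The analyses are exploratory in a trial that says it is unpowered. All of this limits the consequence, and the lack of a missing-data method is not counted here as a fault. What remains is that the article states a contrast rather than staying silent. On its natural reading that contrast is change, and it is extended to the binary outcomes.

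A reader might infer more in two ways, and the article supports neither.

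- **That GEE is biased whenever loss depends on baseline behaviour.** Step 5 shows that it is not. The dependence must also differ by component level, and the size and even the sign then turn on the working correlation and on whose baselines are kept. The article fixes neither.
- **That loss must differ by level because session pay does.** Section 2.7 says "Compensation includes $25 for each workshop session attended", so session pay runs from $25 (one session) to $100 (four). For any single component in a balanced design, however, on averages three sessions and off averages two, a $25 difference. Section 2.13 gives one follow-up payment of $35 and one tracing procedure for everyone. Differential loss is possible but not shown.

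**Conclusion.** The point holds as one of precision and protection against chance imbalance. The change contrast in section 2.15 carries a variance 1/0.65 to 1/0.85 times that of the baseline-adjusted analysis, for assumed ρ of 0.3 to 0.7. This assumes equal variances and a similar correlation at teen and workshop level. Any ρ below 1 favours adjustment. Bias from loss to follow-up is a conditional risk: it needs loss that depends on baseline behaviour differently by component level, and the figures in steps 4 and 5 only illustrate it.

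The primary feasibility and acceptability results are descriptive and unaffected. The reason to act is that these estimates are meant to inform the powered trial, where risky sexual behavior is the expected primary effectiveness outcome, and the same contrast could be carried into it.

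**What to change.** Reword the contrast in section 2.15. For scores, estimate each component effect from the follow-up value with the baseline value as covariate, or from a mixed model on both time points with baseline means constrained equal across conditions. For binary outcomes, use GEE on the follow-up value adjusted for baseline, and name the effect scale (for example, a standardised risk difference). Account for workshop group in both.

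In the same edit, state one scale for risky sexual behavior. Section 2.11.2 has a proportion at follow-up and section 2.15 has a score, and the choice decides which model applies.

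No separate imputation step is needed for this change. Imputing within each workshop would not be workable with about 3.8 teens per group. The cost is a sentence or two and minor programming, with no new data, visits or participants.
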